## Abstract

**Background:**

Social media has become an important tool facilitating communication and connection in a postpandemic landscape. This context has prompted an increase in the sharing of information and disinformation about general health. This provides an opportunity to seek information about and support for intimate (ie, sexual and reproductive) health, with the added assurance of maintaining a degree of anonymity in a socially taboo context.

**Objective:**

The aim of this study is to better understand how women in Aotearoa New Zealand use social media to access sexual and reproductive health information and support. Engagement with stakeholders and community groups will be undertaken throughout the study to analyze the findings and present solutions to identified issues.

**Methods:**

This online survey is the first stage in a study which uses a mixed methods approach involving the collection of qualitative and quantitative data through an anonymous survey on the Qualtrics platform. Recruitment occurred through advertising on the University of Auckland | Waipapa Taumata Rau and University of Waikato social media accounts and physical posters in various locations nationwide. These posters prioritized recruitment of groups that are often underrepresented. This study will also present the preliminary results to stakeholders, prioritizing *whakawhanaungatanga* (building relationships) and *manaakitanga* (kindness and respect for others, emphasizing responsibility and reciprocity) in the co-designing of future research aims. Subsequent analysis of all the above data forms will be performed using reflexive thematic coding analysis, using codes derived from both the literature and emergent from the data. Results will be disseminated in academic, participant, and stakeholder circles. The analysis plan involves research assistants and investigators working collaboratively and independently, progressively comparing codebooks and results to reiteratively code for the eventual thematic results.

**Results:**

Ethical approval to conduct this study was granted by the University of Auckland ethical review board on June 28, 2023, and an amendment to change survey questions and expand recruitment was approved on July 1, 2024. Online data collection closed in February 2025, and focus groups and interviews are scheduled to begin meeting in August 2025 with stakeholder engagement occurring throughout. Compensation was not provided for completion of the online survey, but will be provided (NZ $50 [US $28.93] vouchers) for focus group and interview participants when stage 3 of the project is undertaken.

**Conclusions:**

From early data analysis, we anticipate survey results will confirm our hypothesis that social media communities can provide increased access to information and support for women who have had or continue to have limited access to intimate health care due to a number of factors, including social (embarrassment), structural (location), or cultural (lack of health care provider training) factors.

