Despite appearing on the world stage to be socially progressive in many areas [9], Aotearoa New Zealand has a sexually conservative culture [10,11]. This makes seeking sexual and reproductive health information and support difficult for many. Fear of being judged, feeling shy, embarrassed, or ashamed, not knowing how to access care, and concerns about confidentiality are reported as reasons for unmet needs in sexual and reproductive health care service provision in Aotearoa New Zealand [12]. Adolescents and young adults appear to be the demographic most negatively impacted [12,13]. For Māori, stigma and negative societal attitudes toward sexual health intersect with the systemic racism inherent in Aotearoa New Zealand’s health system [14,15]. All of these combine to negatively impact the way sexual and reproductive health information and support are accessed, as well as the quality of formal health care services provided [12,16]. This stigma intersects with other access barriers, such as cost, transport, and cultural fluency, limiting access to intimate health care. We posit that social media and online communities expand access to intimate health care by providing people with anonymous spaces to discuss and share information that they may not be able to discuss and share within their own communities, or in spaces where they lack anonymity.

In Aotearoa New Zealand, people who are Māori or Pasifika, have a disability, are overweight, or identify as lesbian, gay, bisexual, transgender, *takatāpui*, queer/questioning, intersex, asexual/aromantic/agender, or another marginalized identity (LGBTTQIA+) are more likely to have negative, hostile, and stigmatizing interactions with health care services [17-20]. Moreover, women from these vulnerable populations are more likely to face disparities and inequalities due to multiple levels of existing social injustice [21].

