### Survey Design

The survey (Multimedia Appendix 1) targets women living in Aotearoa New Zealand who have used or use social media resources or communities to access information about sexual and reproductive health care. The survey draws from a convenience sample and asks for respondents who have ever identified or currently identify as women, and/or who were assigned female at birth. The survey asks for respondents who are aged 18 years or older, fluent in English, and live anywhere in Aotearoa New Zealand. The survey does not incorporate the ability to check for duplicate responses; nor does it have strict access controls. We recognize that this may impact the veracity of the results as a stand-alone dataset, but as this online survey is intended to be part of a 3-pronged approach collecting multimodal data, we believe that the data collected will be relevant and valuable in conjunction with the focus groups and individual interviews with known, recruited participants.

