### Stage 1: Online Survey

#### Recruitment Process and Description of the Sample Having Access to the Questionnaire (Contact Mode and Advertising the Survey)

The online survey was an open survey. Participant recruitment occurred through posts from the social media platforms of the Universities of Auckland and Waikato (Figure 1). Funding was allocated to push recruitment among specific population groups that are often underrepresented in online research; these groups are the focus of this study. Physical advertisements of our research were displayed on or in local community notice boards, coffee shops, gyms, libraries, local *marae* (communal and sacred meeting spaces), beauty salons, toilets, and supermarkets nationwide. The physical advertisement is shown in Figure 2. The researchers identified organizations invested in sexual and reproductive health care for sharing digital or poster recruitment flyers. These organizations were recruited as community partners as part of research outreach conducted by members of the research team.

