#### Analysis

To prepare the results of the survey for preliminary analysis and stage 2 of the research, an inclusive approach will be used with incomplete survey questions. After informed consent is provided, all responses will be included, even if the entire survey is not complete. This inclusive approach ensures that all available data contribute to the analysis, enhancing the representativeness of participant experiences and reducing response bias. Given the voluntary nature of participation and the potential for survey fatigue or partial completion, excluding incomplete responses could disproportionately exclude certain groups or perspectives. Including partial data supports equity in research by valuing all contributions and allows for more robust descriptive and exploratory analysis, particularly in early-stage or qualitative-informed research.

As we anticipate that only descriptive statistics will be feasible for the survey data, advanced statistical corrections or inferential analyses are not required at this stage. This is appropriate given the exploratory nature of the study and the likelihood of incomplete responses. The primary objective is to identify patterns and trends in the data to inform stage 2 of the research, rather than to draw generalizable conclusions. Descriptive analysis allows for meaningful insights while respecting the limitations of the dataset.

Questionnaires submitted with an atypical timestamp (eg, unusually fast completion times or submissions outside expected timeframes) will be flagged and reviewed for quality assurance. These cases will not be automatically excluded, but rather assessed contextually to determine if the data appear valid and consistent with other responses. This approach ensures that we do not inadvertently exclude legitimate responses from participants who may complete the survey quickly due to familiarity with the content, while still maintaining data integrity.

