## Discussion

### Anticipated Findings

The Understanding Intimate Health in Online Spaces project aims to better understand the relationship between social media and women’s sexual and reproductive health in Aotearoa New Zealand. We anticipate (from early results [26]) finding that social media plays a significant role in allowing women to seek out information and care that they would otherwise struggle to access, and that this study can help inform clinical practice in community outreach.

A strength of the approach we have described is the meaningful involvement of stakeholders in the interpretation and meaning-making of the survey findings; in-depth interviews and focus groups provided input into the anticipated next phase of the research. This study takes a multidisciplinary approach bringing together researchers from a variety of disciplines, including public health, biostatistics, nursing, and public policy, as well as anthropology and the social sciences. The aim of doing so is to better understand from diverse perspectives how and if social media impacts some of the most intimate aspects of the health of marginalized groups in Aotearoa New Zealand, namely the sexual and reproductive health of women.

A limitation of our survey is that there were few methods used to assure the validity of participant responses. Responses that were clearly copied and pasted from an artificial intelligence tool were automatically excluded, but no questions were integrated as attention checks.

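### The Abstract expects the survey to confirm increased access, but a descriptive survey aimed at past and present users, with no comparator, can only describe perceived access

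*Protocol article*

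**What the plan says.** Three places state an expected effect on access.

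- Abstract, Conclusions: "we anticipate survey results will confirm our hypothesis that social media communities can provide increased access to information and support for women". The sentence goes on to limit this to women whose access to intimate health care is or has been limited.
- Introduction: "We posit that social media and online communities expand access to intimate health care".
- Discussion, Anticipated Findings: "social media plays a significant role in allowing women to seek out information and care that they would otherwise struggle to access".

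The Methods describe a more modest exercise.

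- Survey Design: the survey "targets women living in Aotearoa New Zealand who have used or use social media resources or communities to access information" on sexual and reproductive health, and "The survey draws from a convenience sample".
- Stage 1, Recruitment Process: "The online survey was an open survey". It was advertised through university social media accounts and through physical posters.
- Stage 1, Analysis: only descriptive statistics are expected to be feasible, inferential analysis is judged unnecessary at this stage, and "The primary objective is to identify patterns and trends in the data to inform stage 2 of the research, rather than to draw generalizable conclusions".
- Data Analysis: quantitative answers are summarised descriptively. Qualitative answers go into a reflexive thematic analysis together with the material from stages 2 and 3.

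The research question in the Introduction asks how women use social media for this purpose. It then asks about both the advantages and the disadvantages they perceive.

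**The concern.** Increased access is a comparison: access with social media against access without it, for the same or similar women. The Discussion makes the second arm explicit by referring to care that women would otherwise find hard to reach. A survey aimed at people who already use, or once used, social media for this purpose describes one side of that comparison. Descriptive summaries do not supply the other.

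What is at stake is the conclusion the study will be allowed to draw. The confirmatory sentence stands in the Abstract, which is the part most often read alone. The Discussion also suggests that the study can help inform clinical practice in community outreach. If the results are written up as confirmation, readers will take an exploratory description of self-selected respondents for evidence of an effect. The research question gives disadvantages equal standing, and the pilot work cited in the Introduction found signs of embarrassment, shame and stigma in social media use. The two anticipated conclusions mention benefit only.

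**Working it through.** The article states no sample size calculation, test or error rate, so there is no figure to reproduce. The check sets the claim beside the design.

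1. **What confirmation would need.** Write A1 for a woman's access to information and support with social media and A0 for her access without it. The hypothesis is A1 − A0 > 0, at least for women with limited access to care. Confirming it needs information on both terms, and a statement of which results would count against it.

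2. **What the survey observes.** The study is cross-sectional (Methods, Overview). Its target is women who "who have used or use social media resources or communities to access information about sexual and reproductive health care". Their answers bear on A1, and possibly on how they themselves perceive the difference. The article describes no non-user group and no earlier time point that would supply A0.

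3. **What the analysis does.** It gives descriptive statistics for closed questions and thematic coding for open ones. Neither is set up as a comparison. No pattern of answers is named under which the hypothesis would be judged unsupported.

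4. **Whether later stages fill the gap.** Stage 2 presents findings to stakeholders for interpretation. Stage 3 pilots a focus group and interview guide with about 5 to 8 participants and expressly does not aim for saturation. Neither adds a comparator.

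5. **Whether sample size helps.** Survey Administration reports about 500 recorded responses, of which about 320 were complete and eligible. For illustration only, assume simple random sampling and a proportion of 50%. The 95% half-width is 1.96 × √(0.5 × 0.5 / n):
   - n = 320: 1.96 × √(0.25 / 320) = 1.96 × 0.0280 ≈ 0.055, or 5.5 percentage points
   - n = 500: 1.96 × √(0.25 / 500) = 1.96 × 0.0224 ≈ 0.044, or 4.4 percentage points

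   This is precision for a proportion among respondents. A convenience sample does not meet the sampling assumption, and no value of n turns a proportion among respondents into an estimate of A1 − A0.

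6. **Side by side.** The Abstract anticipates confirmation of a hypothesis. The Analysis section describes an exploratory study that looks for patterns to inform the next stage and declines generalizable conclusions. The second is consistent with the design and the first is not.

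**The case against.** The strongest reply is that the wording is softer than a claim of effect. The authors anticipate rather than assert. They say that communities can provide increased access, and they confine this to women with limited access to care. Accounts from users may well support a statement that such access is possible for some women. The study is also mixed-methods, its main question is how women use social media, and a causal standard is arguably out of place. The Analysis section already disclaims generalizable conclusions, and Survey Design admits doubts about the survey as a stand-alone dataset. The questionnaire (Multimedia Appendix 1) is not shown, so it may ask about earlier access or about where respondents would otherwise have gone.

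Much of this stands. It shows that the plan does not claim a population effect and that the Methods are candid. It does not rescue the word confirm. Self-reports can illustrate that social media helped some respondents. Questionnaire items on alternatives would still give uncontrolled perceptions of A0. Holding the study to a descriptive standard is what the Analysis section asks for, and the Abstract and Discussion depart from it.

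**Conclusion.** The point holds as an inconsistency between the anticipated conclusions and the plan. The survey can describe perceived access, advantages and disadvantages among respondents, but it cannot confirm that access is increased. No numerical bias can be attached to this from the documents. The effect is on what the study may conclude, and no dataset or planned analysis changes. The verdict assumes that confirm carries its ordinary meaning and that the unseen questionnaire contains no external comparator.

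A reader might infer more than the article supports:

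- *That the only limit on generalizability concerns other countries.* The Discussion's Conclusions mention only that one, but the Analysis section disclaims generalizable conclusions outright.
- *That the hypothesis was formed after looking at the data.* In the Abstract, early analysis informs the anticipation. The Introduction argues the hypothesis from literature on stigma and barriers to access.
- *That women who gave up on social media are absent.* Past users are expressly part of the target.
- *That all of the roughly 320 complete eligible responses come from users.* The itemised criteria (sex or gender, age, English, residence) do not list social media use, and posters were also used, so some non-users may have answered. No comparison with them is planned.
- *That a favourable result is close to guaranteed.* Users can report that social media was useless or harmful.

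**What to change.** 1. In the Abstract's Conclusions and in the Discussion's Anticipated Findings, replace the confirmatory and counterfactual wording with a descriptive statement. For example: *the survey will describe the advantages and disadvantages that respondents who use or have used social media for sexual and reproductive health information and support perceive in doing so, including its perceived role in access.* Name both advantages and disadvantages, as the research question does.
2. In the Discussion's Conclusions, repeat the disclaimer from the Analysis section. Add that the sample is self-selected and aimed at users, so it does not estimate use or benefit among women in Aotearoa New Zealand generally.

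The Introduction's statement of the hypothesis can remain as motivation. The Discussion's open question of whether and how social media affects intimate health can also stay, since it describes the wider project and presupposes no answer.

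The cost is a less favourable stated conclusion. No new data or analysis is needed.

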**International Registered Report Identifier (IRRID):**

DERR1-10.2196/65288

## Introduction

During the COVID-19 pandemic, social media peaked as a major tool for communicating health information and connecting people to each other during a time of physical distancing; it was widely used by public health professionals and conspiracy theorists alike [1]. Since the beginning of the COVID-19 pandemic, the use of social media for obtaining health information and support on all kinds of health-related topics has increased [2]. The use of social media to convey information and provide support in relation to socially taboo topics, specifically sexual and reproductive health, will be further investigated in this study. We focus on the experiences of women living in Aotearoa New Zealand, and their use of social media for sexual and reproductive health information and support. We define social media as any online environment that builds relationships and facilitates connection as well as the sharing of information and lived experiences of those who use it. Textbox 1 provides definitions of important local terms.

Local terms of referenceHui: a meeting, workshop, or gathering.Kanohi ki te kanohi: face-to-face interaction; a culturally significant approach in Māori contexts that emphasizes the importance of personal connection, presence, and direct engagement.Koha: a gift or offering used to acknowledge a contribution, grounded in principles of reciprocity and care for others.Māori: the Indigenous people of Aotearoa New Zealand.Manaakitanga: the expression of care, hospitality, and kindness toward others, upholding their dignity and well-being.Marae: a communal and sacred meeting space that serves as the focal point for Māori social, cultural, and spiritual life, typically including a meeting house (wharenui) and other associated buildings.Takatāpui: a traditional Māori term that has been reclaimed to describe a person who is Māori and identifies with diverse genders and/or sexualities, encompassing both cultural and LGBTQIA+ identities.Te reo Māori: the Māori language, an official language of Aotearoa New Zealand and a cornerstone of Māori identity, culture, and heritage.Whakawhanaungatanga: the process of building and maintaining relationships through shared connections, trust, and mutual respect.

Sexual health is a state of complete physical, emotional, spiritual, mental, and social well-being regarding sexuality, sexual orientation, sexual expression, and gender identity [3]. It also encompasses the ability of a person to have safe and pleasurable sexual experiences [3]. Reproductive health extends this definition and focuses on a complete state of well-being in relation to the body’s reproductive system and processes [3]. Reproductive autonomy is a core feature of this definition, as people must have autonomy over whether, when, and by what means they have a child [3]. The achievement of optimal sexual and reproductive health is dependent on environments that affirm, promote, and respect health for all individuals regardless of their sex assigned at birth or their gender [3]. This includes environments that allow individuals timely access to comprehensive, high-quality, and unbiased information, where they are free from coercion and discrimination [3].

The COVID-19 pandemic accentuated the crucial role of social media in information dissemination. Social media can be an effective communication tool in times of crisis, as the need to quickly disseminate information is particularly pressing [4]. Equally, the interactive nature of social media allows individuals to seek support from others. Social media provides opportunities for connection, identity formation, and a sense of group belonging [5,6]. Online communities on social media provide resources for individuals in relation to sexual and reproductive health information and support [7]—topics that are often shrouded in embarrassment and shame [8].

Despite appearing on the world stage to be socially progressive in many areas [9], Aotearoa New Zealand has a sexually conservative culture [10,11]. This makes seeking sexual and reproductive health information and support difficult for many. Fear of being judged, feeling shy, embarrassed, or ashamed, not knowing how to access care, and concerns about confidentiality are reported as reasons for unmet needs in sexual and reproductive health care service provision in Aotearoa New Zealand [12]. Adolescents and young adults appear to be the demographic most negatively impacted [12,13]. For Māori, stigma and negative societal attitudes toward sexual health intersect with the systemic racism inherent in Aotearoa New Zealand’s health system [14,15]. All of these combine to negatively impact the way sexual and reproductive health information and support are accessed, as well as the quality of formal health care services provided [12,16]. This stigma intersects with other access barriers, such as cost, transport, and cultural fluency, limiting access to intimate health care. We posit that social media and online communities expand access to intimate health care by providing people with anonymous spaces to discuss and share information that they may not be able to discuss and share within their own communities, or in spaces where they lack anonymity.

In Aotearoa New Zealand, people who are Māori or Pasifika, have a disability, are overweight, or identify as lesbian, gay, bisexual, transgender, *takatāpui*, queer/questioning, intersex, asexual/aromantic/agender, or another marginalized identity (LGBTTQIA+) are more likely to have negative, hostile, and stigmatizing interactions with health care services [17-20]. Moreover, women from these vulnerable populations are more likely to face disparities and inequalities due to multiple levels of existing social injustice [21].

Women’s sexual and reproductive health in Aotearoa New Zealand is of particular relevance due to the high incidence of sexually transmitted infections (STIs) in comparison to other Western countries [10,11]. National STI rates in Australia, the United States, and the United Kingdom are lower than regional STI rates in Aotearoa New Zealand [10]. Women in sexual relationships with male partners older than themselves may be particularly at risk of contracting an STI [11]. Other intimate health concerns include the long-term mental and physical impacts of untreated STIs, such as infertility and ectopic pregnancy [12,22], and the incidence of cervical cancer, which is often not adequately screened for in Aotearoa New Zealand [23].

For this study, we have chosen to define women as those who were assigned female at birth, and/or anyone who has ever self-identified or currently self-identifies as a woman. Upon consultation with extended networks, we acknowledge this inclusive definition will not be favored by everyone [24]. Defining gender and sexuality is an active space, and we recognize that these concepts are ever-evolving and that descriptions can and do change over time. Grounded in the underlying philosophical paradigm of intersectional feminism [25], this study’s research question is as follows: In the context of women’s experiences of the Aotearoa New Zealand health system, how do women use social media to find information and support around sexual and reproductive health?

Further, we ask what advantages and disadvantages they perceive regarding such social media use. The findings from pilot testing the survey [26] suggest that that individuals may find benefit from social media, as well as encounter feelings of embarrassment, shame, and stigma in their use of social media for sexual and reproductive health information and support.

